### Recruitment

Study advertisements will invite POWH staff to sign up for the 12-week study and notify them that participants will be randomly assigned to one of two conditions, labeled *online presentations* and *take-home readings*. Those assigned to the former condition will be the intervention group, and those assigned to the latter condition will be the active control group. Once assigned, the participants will know whether they are in the *online presentations* or *take-home readings* condition, but they will be blind to which condition is the true intervention versus the active control. They will also be assured that all participants in one version of the Thrive program will receive all the resources of the other version after the end of the 12-week study period. This assurance should reduce the incentive for participants in one group to share any course content with a participant from the other group (the participants will also be explicitly instructed not to share anything with anyone else throughout the program).

Potential participants will be informed that those who complete the Thrive program will be eligible to receive Continuing Professional Development (CPD) points. At POWH, nurses and other health care workers are expected to engage in ongoing professional development by attending workshops, completing courses, and participating in other such activities, with a certain number of CPD points awarded for each activity. Each worker has to earn at least 20 points per year, and each Thrive participant will receive 10 points after completing the program. As the control participants will gain access to the full Thrive program at the end of the 12-week study period, all the participants will receive 10 points regardless of the condition to which they are assigned. There are numerous ways outside the Thrive program in which a given health care worker can earn their required CPD points, so the offer of 10 points for completing the program is not an undue inducement to participate but rather fair compensation for the participants’ time and effort. Each participant will also receive a Certificate of Completion from the research team.

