### Randomization and Informed Consent

Hospital staff interested in participating will sign up for the study by writing their details (ie, name, email address, and ward) on registration sheets posted around the wards, by registering on the web via the hospital’s professional development website, or by emailing a designated member of the research team (MM). The final list of participants will be sorted according to ward to allow for stratified randomization. For each ward, a random number generator will be used to allocate half the participating staff to the intervention condition and half to the active control condition. Next, the participants will be notified by email as to the condition to which they have been assigned. This email will also provide the Participant Information Statement and Consent Form and a link to the first survey. After reading the form, those who are willing to participate will click on the link to access the first survey. The first item of this survey provides a button whereby the participant can digitally record their consent to participate. For the remainder of the study period, the participants will be sent the relevant survey links and program resources by email at the appropriate times.

All participants will be free to withdraw at any time from the surveys, the Thrive program, or both the surveys and the program without penalty and without having to give a reason, with the provision that only those who complete the Thrive program will receive the 10 CPD points and Certificate of Completion. However, completion of the surveys will not be required to earn the points and certificate. In other words, if a participant is enjoying the program and wishes to finish it but does not want to continue providing data via the surveys, they will be welcome to do so.

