### Anonymity and Confidentiality

Although each participant will provide their name, email address, and ward to enroll in the Thrive program, their survey responses will be completely anonymous and linked via a participant code number. At each measurement occasion, the participants will be emailed a link to the survey and, when they click on the link, they will be taken to the web-based Qualtrics (Qualtrics International Inc) platform that will be hosting the surveys. The web-based surveys will not ask for any information that could be used to identify any individual participant, and Qualtrics will not record any metadata from the respondents either. To match each participant’s responses on one measurement occasion with their responses on the other occasions, each survey will ask the respondent to provide a self-generated code. The respondent will be instructed to take the last 3 digits of their mobile phone number and the last 2 digits of their birth year to create their own 5-digit code. For example, if a participant’s phone number ended in the digits *123* and they were born in 1970, their code would be *12370*. One might argue that someone familiar with a given participant could identify their survey responses from this code, but none of the researchers who will have access to the raw data will be personally acquainted with any of the participants. Furthermore, once all the data have been collected and all the responses have been matched, the 5-digit codes will be deleted from the data set and replaced with generic, arbitrary ID numbers.

At each measurement occasion, the survey link sent to the intervention participants will be different from the link sent to the active control participants (even though the surveys themselves will be identical). This will allow the researchers to keep track of which condition each participant is in without relying on self-reports.

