### Analysis

Missing values in the data set will be estimated via multiple imputation, and the initial analyses will be conducted on an intention-to-treat basis followed by per-protocol analyses to account for levels of treatment compliance (eg, program attendance). The data will be analyzed via a linear mixed model that will allow the group-by-time interaction effects to be estimated. It is hypothesized that levels of well-being will increase over time in the intervention condition relative to the active control condition. Similarly, it is hypothesized that levels of psychological distress (ie, symptoms of depression, anxiety, and stress) will decrease over time in the intervention condition relative to the active control condition. There may also be a group-by-time interaction effect on one or more of the secondary outcomes. For example, the intervention may promote increased compassion, mindfulness, or work engagement. Furthermore, any interaction effect may itself be moderated by a variable such as resilience or coping style (cf [9,31]).

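### Participants learn their condition before they consent and answer the baseline survey, so entry to the trial and the baseline values can depend on the arm

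*Protocol article*

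**What the plan says.** The order of steps is set out in the protocol article, Methods, Randomization and Informed Consent. Staff sign up with name, email address and ward. The list is sorted by ward and randomised half and half within each ward. Then: "Next, the participants will be notified by email as to the condition to which they have been assigned". On the same message: "This email will also provide the Participant Information Statement and Consent Form and a link to the first survey". The entry decision follows: "After reading the form, those who are willing to participate will click on the link to access the first survey". Consent is recorded inside the baseline survey: "The first item of this survey provides a button whereby the participant can digitally record their consent to participate".

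Two other sections agree with this order. Recruitment states: "Once assigned, the participants will know whether they are in the *online presentations* or *take-home readings* condition". Anonymity and Confidentiality says that, at each measurement occasion, "the survey link sent to the intervention participants will be different from the link sent to the active control participants", which requires allocation to exist before survey 1 goes out.

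Under Analysis, missing values are to be multiply imputed and "the initial analyses will be conducted on an intention-to-treat basis", with group-by-time effects estimated in a linear mixed model. Sample Size gives 69 completers per group, raised to 99 per group for up to 30% attrition by the last survey, and a target of at least 200.

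**The concern.** Randomisation protects the comparison only among people whose presence in the data does not depend on their arm. Here a person who has signed up learns the format first and then chooses whether to consent and answer survey 1. The formats differ visibly: seven one-hour webinars with reflective sheets, against weekly infographic documents. Someone disappointed by the readings, or put off by the webinar hours, can leave at that point without giving any data.

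Three things are at stake.

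- **Analysis set.** In practice the intention-to-treat analysis can cover only those who accepted the arm they were given.
- **Baseline.** Survey 1 is the reference for every group-by-time contrast. COMPAS-W and DASS-21 are self-reported, and they are answered with the format known.
- **Sample size.** Refusals between allocation and survey 1 may not be covered by the 30% allowance.

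**Working it through.** **1. What follows disclosure.** By the text the sequence is sign-up, randomisation within ward, email naming the condition (with consent form and survey link), decision to proceed, consent as first survey item, baseline answers. The last three steps all come after the arm is known. This needs no inference.

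**2. What is known about a decliner.** Name, email and ward come from registration, and the arm comes from the allocation list. The arm-specific links also allow survey 1 entries to be counted by arm. What is missing is consent, every baseline covariate collected by survey, and every outcome. Survey answers are linked only through a self-generated code. An imputation model would have ward and arm alone to work from.

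**3. The plan's own figures.** Repeated-measures ANOVA, within-between interaction, with the inputs in Sample Size: partial η² = 0.01, so f² = 0.01/0.99; m = 4 occasions; correlation ρ = 0.5; α = 0.05; sphericity. Noncentrality λ = f²·N·m/(1 − ρ), degrees of freedom 3 and 3(N − 2).

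- N = 136: power 79.9%.
- N = 138 (69 per group): power 80.6%.
- 69/0.7 = 98.6, rounded up to 99 per group.

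The stated 69 and 99 are reproduced.

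**4. Difference in level from selective entry (uptake and gaps are assumptions).** In one arm, acceptor mean minus the mean of all randomised = (1 − uptake) × gap, where gap is acceptors minus decliners in SD.

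- Uptake 90%/80%, gap 0.3: 0.20 × 0.3 − 0.10 × 0.3 = 0.06 − 0.03 = 0.03 SD.
- Uptake 95%/75%, gap 0.5: 0.25 × 0.5 − 0.05 × 0.5 = 0.125 − 0.025 = 0.10 SD.

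A second model, with non-selective entry in one arm and logistic entry in the other, gives about 0.04, 0.10, 0.14 and 0.19 SD. The assumed entry rates are 85%, 80%, 70% and 60%, with log-odds slopes of 0.3, 0.5, 0.5 and 0.5 per SD. If declining is unrelated to the score, the expected difference is 0 whatever the rates.

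**5. What reaches the planned contrast.** The planned effect is group by time, not level. If entry depends on the baseline score, a baseline difference d has expected follow-up value ρ·d with no treatment effect. The change contrast is then ρ·d − d = −(1 − ρ)·d. With ρ = 0.5 its size is d/2: 0.03/2 = 0.015 SD and 0.10/2 = 0.05 SD. If entry depends on a stable trait, the difference is the same at both times and cancels.

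**6. Effect on power, if the 200 is counted at randomisation.** Completers = 200 × (1 − refusal) × 0.7. Number to randomise per arm = 69/0.7/(1 − refusal), rounded up. Refusal rates are assumed.

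- 0%: 140 completers, power 81.2%; 99 per arm.
- 5%: 133, taken as 132, power 78.6%; 104 per arm.
- 10%: 126, power 76.5%; 110 per arm.
- 20%: 112, power 70.8%; 124 per arm.
- 30%: 98, power 64.3%; 141 per arm.

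Both uptake scenarios in step 4 lose 15% on average, so they fall between the 10% and 20% lines.

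**The case against.** The protocol contains real safeguards. Advertisements name both formats and the random assignment before anyone signs up. Eligibility requires willingness to complete the program and all four surveys. Participants are blind to which format is the true intervention. Each arm later receives the other arm's resources, and everyone can earn the same 10 CPD points. Survey 1 precedes any program content, and baseline COMPAS-W asks how people feel most of the time, a frame less open to a shift from knowing the arm. The two motives for leaving, disappointment and burden, can also act in opposite arms and partly offset.

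This lowers the risk and argues against the highest severity, but it does not remove the risk. The masking does not hide the format itself. Later access is offered as a deterrent to sharing content. The CPD points do not depend on answering surveys, so a person can skip them at no cost.

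A reader might infer three stronger things that the documents do not support:

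- *That the set is self-selected by arm.* No refusal rate is given for either arm; it can be, and no more can be said.
- *That decliners leave no trace.* They have a recorded sign-up, ward and allocation. Their data are missing because they did not consent; anonymity is not the cause.
- *That 0.10 SD is the bias in the treatment effect.* It is an assumed difference in level, and about half of it or less reaches the change contrast under the two mechanisms in step 5. Selection on expected response could bias that contrast differently, but nothing in the document allows it to be sized.

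**Conclusion.** The point holds as a weakness in sequencing. Entry and the self-reported baseline follow disclosure of the delivery format, so the analysable set can differ by arm in ways that the planned analysis cannot undo.

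Its size and direction are unknown. The illustration of 0.03 to 0.10 SD in level, and about 0.015 to 0.05 SD in change, rests on assumed uptake, assumed gaps, entry that depends on the baseline score, and the protocol's correlation of 0.5. No figure is offered for a reporting shift at baseline.

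The loss of power is conditional. Sample Size speaks of recruiting 99 per group and does not say whether that counts people at allocation or at consent. If at allocation, refusals before survey 1 may add to the 30%, unless that figure is meant to include them.

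Severity: should-fix. The likely bias is modest, but it cannot be repaired once a cohort has enrolled, and it is cheap to prevent in those still to come.

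**What to change.** **Remaining wards (invited October to December 2021).** Split the email. Send the consent form and survey 1 in a neutral message that does not name the condition. The arm-specific link can stay, provided nothing in it reveals the format, so anonymous tracking of the arm still works. Send the allocation notice only after survey 1 closes. Define the intention-to-treat set as all who consented and completed survey 1 before notification, analysed as allocated. People lost before that point would then be lost without knowing their arm. State that the target of 200 counts this set.

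**First five wards (already run).** The order cannot be changed. Report sign-ups allocated, consents and survey 1 completions by arm, using the registration list and the arm-specific links. Show results by wave as a sensitivity analysis.

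**Cost.** One extra email, notification delayed by a few days within week 0, and whatever ethics amendment the change requires. Program content, measures and the calculated 69 and 99 per group are unaffected.

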### Sample Size

Power calculations suggest that at least 200 participants need to be recruited (100 per condition) to detect a small group-by-time interaction effect at 80% power. This sample size was calculated using the statistical software package G*Power (version 3.1.9.2) [32,33]. Assuming a small effect of 0.01 (partial *η*^2^), a conventional type-1 error rate of 0.05, and a correlation of 0.5 among the repeated outcome measures, the study will be able to detect such an effect at 80% power with 69 participants in each group. However, considering an attrition rate of up to 30% by the final measurement occasion, it will be necessary to recruit at least 99 people per group, so we will aim for a total sample size of at least 200. The projected attrition rate of 30% is based on the attrition rates reported in previous RCTs [23-25] that examined interventions to increase well-being in hospital staff. Additional power calculations show that the study will be able to detect effects as small as 0.04 (partial *η*^2^) even under the strictest nonsphericity correction and possible attrition of up to 65%.

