**Results:**

The Thrive program was delivered to a small number of wards at the hospital between February 2021 and July 2021, and it will be delivered to the remaining wards from October 2021 to December 2021. A power calculation has recommended a sample size of at least 200 participants in total. A linear mixed model will be used to estimate the interaction effects.

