## Methods

### Design

The Thrive program will be evaluated in an RCT with 2 conditions and 4 measurement occasions. Thus, there will be two main independent variables—one between-group factor and one repeated-measure factor—as well as a selection of covariates and dependent variables. The two conditions will be the intervention (ie, the Thrive webinar program) and an active control condition (only an abbreviated pamphlet version of the educational components of the program). The study will take place over a 12-week period, and a web-based survey will be administered at each of the 4 measurement occasions. In week 0 (ie, 1 week before the program commences), the participants will complete the baseline survey (before the intervention). The Thrive program (and the parallel active control program) will run for 7 weeks, from week 1 to week 7. The participants will complete the second survey in week 4 (at the midpoint of the program), the third survey (after the intervention) in week 8 (ie, 1 week after the conclusion of the program), and the fourth survey (follow-up) in week 12 (ie, 4 weeks after the intervention). Each survey will take approximately 20 to 30 minutes to complete. Once all 4 surveys have been administered and the study period has concluded, all the participants in the active control condition will be given access to the full version of the Thrive program. The study timeline is illustrated in Figure 1.

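### The 80% power claimed for a partial eta-squared of 0.01 holds only on a different effect-size scale; on the stated metric, 69 per group detects about 0.026 and has about 37% power at 0.01

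*Protocol article*

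**What the plan says.** The Sample Size section of the protocol article sets the target at 200 participants "to detect a small group-by-time interaction effect at 80% power". The inputs are all given there: "Assuming a small effect of 0.01", labelled as partial eta-squared; "a conventional type-1 error rate of 0.05"; and "a correlation of 0.5 among the repeated outcome measures". The software is named as G*Power 3.1.9.2. The Design section supplies the layout: "The Thrive program will be evaluated in an RCT with 2 conditions and 4 measurement occasions".

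From these inputs the section concludes that "the study will be able to detect such an effect at 80% power with 69 participants in each group". It inflates 69 to 99 per group for 30% attrition and rounds up to 200 in total. It adds that effects down to a partial eta-squared of 0.04 could be detected with up to 65% attrition and the strictest nonsphericity correction. The abstract carries the result forward: "A power calculation has recommended a sample size of at least 200 participants in total".

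**The concern.** Partial eta-squared for a within-between interaction is SS_interaction/(SS_interaction + SS_error). The error term is the within-person residual, so the correlation between occasions is already reflected in it. A calculation that takes such a value and then also multiplies by a factor built from that correlation credits the repeated-measures gain twice.

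If that is what produced 69, the stated power does not belong to the stated effect. Readers will compare the planned 0.01 with the partial eta-squared estimated from the trial data. On that comparison the protocol promises a sensitivity that the design does not have, and a non-significant interaction would seem more informative about small effects than it is.

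**Working it through.** **Inputs.** From the Sample Size section: partial eta-squared 0.01, alpha 0.05, correlation rho = 0.5, 69 per group (N = 138), attrition 30%. From the Design section: k = 2 groups, m = 4 occasions. Assumed: sphericity (epsilon = 1) for the main figure, since the section mentions a correction only for the second statement. The test is the omnibus interaction, noncentral F on 3 and 3(N − 2) df.

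**1. Reproducing the plan's figure.** f² = 0.01/0.99 = 0.0101, so f = 0.1005. Take lambda = f² × N × m/(1 − rho) = f² × N × 8.
- N = 136: lambda = 10.99, power 0.799.
- N = 138: lambda = 0.0101 × 138 × 8 = 11.15, df 3 and 408, power 0.806.

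The smallest balanced N reaching 80% is 138, that is 69 per group. Then 69/0.7 = 98.6, so 99. The plan's arithmetic reproduces exactly.

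**2. What that effect is as a partial eta-squared.** Lambda/(lambda + error df) = 11.15/(11.15 + 408) = 0.0266. The large-sample form, 8f²/(8f² + 3), gives 0.0262. The effect powered is therefore about 0.026 to 0.027.

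**3. Power when 0.01 is a true partial eta-squared.** The correlation is already in the error term, so lambda = f² × (N − 2) × (m − 1).

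| Completers | lambda | Power |
|---|---|---|
| 138 | 0.0101 × 136 × 3 = 4.12 | 36.5% |
| 200 (no attrition) | 0.0101 × 198 × 3 = 6.00 | 51.5% |
| 364 (182 per group) | 0.0101 × 362 × 3 = 10.97 | 80.1% |

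Minor variants of lambda give 36.5% to 37.0% at N = 138. A simulation of 20,000 trials (69 per arm, equal correlations of 0.5) gave 36.9% for a true 0.01 and 80.8% for the effect the plan powered. The smallest partial eta-squared with 80% power at N = 138 is 0.0263.

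**4. The 0.04 sentence.** With 65% attrition, N = 0.35 × 200 = 70. The strictest correction for four occasions is epsilon = 1/3, so df are 1 and 68. f² = 0.04/0.96 = 0.0417.
- Plan's scale: lambda = 0.0417 × 70 × 8/3 = 7.78, power 78.5%.
- Stated metric: lambda = 0.0417 × 68 × 3/3 = 2.83, power 38.2%.
- Detectable at 80% on the stated metric: about 0.11.

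Both statements fit the same scaling.

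**5. Translation to SD units (illustration only).** With between-arm gaps d_j at the four occasions in SD units, f² = mean of (d_j − d̄)² divided by 4. For gaps 0, d/2, d, d this is 0.04297d², so f² = 0.0101 gives d = 0.485 at week 8 (0.48 at exactly 80% power). Other shapes give 0.36 SD (linear growth) to 0.57 SD (rise, then half lost by week 12). The document gives no time course, so none of these is the plan's own figure.

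**6. A different test, for reference.** A 1-df contrast at week 8 with 69 per arm and rho = 0.5 has 80% power for about 0.48 SD on change scores and about 0.42 SD with baseline as covariate. That the first figure matches the 0.48 in step 5 is a coincidence of the assumed shape.

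**The case against.** The strongest reply is that nothing has been miscalculated. Every number in the section reproduces, the software accepts an effect on this scale, and the correlation of 0.5 is disclosed, so a careful reader can recover the calculation. If the authors meant f of about 0.10 relative to the within-cell SD, N stands and only a label is off. This is right as far as it goes: a reader who infers an arithmetic slip, or that 200 is the wrong target and must be raised, goes beyond what the document supports. It does not rescue the sentence, because the section names partial eta-squared and attaches 80% power to 0.01 on it.

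A second reply concerns SD units. A reader might infer that the trial can reliably detect only about half an SD at week 8. The document does not support that: the figure needs a time course it does not state, and plausible shapes span 0.36 to 0.57 SD. Nor should partial eta-squared of 0.026 be equated with 0.48 or 0.42 SD at week 8 as if these were one quantity, since those contrast figures belong to a 1-df test and 0.026 to a 3-df test.

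Third, 138 completers is a conservative basis for the primary end point. The 30% attrition is projected to the final occasion (week 12), the primary end point is week 8, and the analysis is an intention-to-treat mixed model with multiple imputation. With 100 per arm, the baseline-adjusted week-8 contrast would detect about 0.345 SD. This stands, but it concerns a test the section did not power.

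Finally, the 0.04 sentence states no power level, so its 78.5% is not a separate error; it repeats the same labelling problem. And the Analysis section plans no equivalence claim, so misreading of a null result is a risk, not something the protocol commits to.

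**Conclusion.** The point holds as a mismatch between the named effect-size metric and the calculation behind it. As written, 80% power for a partial eta-squared of 0.01 with 69 per group is wrong: it is about 37% with 138 completers and about 52% with 200, and 80% would need about 364. What 138 completers do provide is 80% power for about 0.026. On the same metric the 0.04 claim has about 38% power, with about 0.11 detectable at 80%.

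These results rest on the document's alpha, correlation and layout, on equal correlations with sphericity for the main figure, and on the omnibus interaction that the section itself powers. They need no assumed trajectory. The finding does not show that the sample size is unsuitable, and it fixes no detectable difference in SD units. It should be corrected because the trial's only stated power figure is untrue on its own terms and can be put right at no cost.

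**What to change.** Keep N = 200 and reword the Sample Size section:

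- State that about 138 completers give 80% power at alpha 0.05 on the 3-df omnibus group-by-time interaction for a partial eta-squared of about 0.026, equivalently f = 0.10 on the within-cell SD scale with correlation 0.5.
- Remove the claim of 80% power for a small partial eta-squared of 0.01.
- Restate the 0.04 sentence on the same metric: with 70 completers and the lower-bound correction, about 0.11 is detectable at 80% power, and 0.04 has about 38%.
- If an SD translation is wanted, give it as an illustration with its assumed trajectory, for example 0.48 SD at week 8 for gaps of 0, d/2, d, d, and 0.36 to 0.57 SD across other shapes.
- If sensitivity at the week-8 end point is wanted, report it separately as a 1-df contrast: about 0.48 SD for change scores and about 0.42 SD with baseline adjustment at 69 per arm.

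The cost is wording only. No participants, outcomes or analyses change; the stated sensitivity becomes less favourable.
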